### 2.3.1 EFFECTIVENESS OF INTERVENTION MODULE IN IMPROVING KAP ON OSH AMONG FOOD HANDLERS

*There were also limited studies that specifically look into the effectiveness of intervention module in improving KAP on occupational safety and health among food handlers. There were more studies that look into the effectiveness of an intervention module in improving KAP on food safety and food hygiene among food handlers. Thus, due to the limitation the literature review on the effectiveness of intervention module in improving KAP on occupational safety and health among food handlers also include study that examine the effectiveness of an intervention module in improving KAP on food safety and food hygiene among food handlers. The summary of the findings is tabulated in the table below:*

| Variable | Reference               | Study Details                                                                                                                                                        | Findings                                                                                                                                                            | p value |
|-----------------|--------------------------------|-----------------------------------------------------------------------------------------------------------------------------------------------------------------------------|----------------------------------------------------------------------------------------------------------------------------------------------------------------------------|----------------|
| Knowledge       | (Adamu et al., 2021)           | Impact of An Intervention Program on Improvement of Knowledge, Attitudes, Practices (KAP) On Food and Occupational Health Safety Among Cattle Abattoir Workers in Malaysia. | Comparison of score in pre and post- intervention phases indicated a significant difference in knowledge.                                                                  | p<0.0001       |
| Knowledge       | (Isara & Isah, 2009)           | Knowledge and practice of food hygiene and safety among food handlers in fast food restaurants in Benin City, Edo State                                                     | Knowledge was significantly influenced by previous training in food hygiene and safety.                                                                                    | p = 0.002      |
| Knowledge       | (Mohd Ishanuddin et al., 2019) | An Investigation of Knowledge, Attitude and Practice of Occupational Safety and Health (OSH) on Safety Climate at Workplace in Manufacturing Industry                       | If knowledge of workers about safety is high, the workers perception towards supervisor's commitment in relation to comply with safety and health regulation is also high. | p < 0.01       |

|           |                                |                                                                                                                                                                             |                                                                                                                                                                                                     |             |
|-----------|--------------------------------|-----------------------------------------------------------------------------------------------------------------------------------------------------------------------------|-----------------------------------------------------------------------------------------------------------------------------------------------------------------------------------------------------|-------------|
| Knowledge | (Has et al., 2018)             | An Assessment on Pre- and Post-Food Hygiene Training on Food Safety's KAP Level Among Food Handlers In Kuala Terengganu And Kuala Nerus                                     | There was a significant difference in knowledge scores pre- and post-food hygiene training.                                                                                                         | $p < 0.05$  |
| Attitude  | (Adamu et al., 2021)           | Impact of An Intervention Program on Improvement of Knowledge, Attitudes, Practices (KAP) On Food and Occupational Health Safety Among Cattle Abattoir Workers in Malaysia. | Comparison of score in pre and post- intervention phases indicated a significant difference in attitude (0.025) but no significant difference was observed in practice scores ( $p = 0.115$ ) based | $p = 0.025$ |
| Attitude  | (Mohd Ishanuddin et al., 2019) | An Investigation of Knowledge, Attitude and Practice of Occupational Safety and Health (OSH) on Safety Climate at Workplace in Manufacturing Industry                       | The attitude on safety at the workplace have no significant correlation with practices.                                                                                                             | $p = 0.616$ |
| Knowledge | (Has et al., 2018)             | An Assessment on Pre- and Post-Food Hygiene Training on Food Safety's KAP Level Among Food Handlers in Kuala Terengganu And Kuala Nerus                                     | There was no significant difference in attitudes scores pre- and post-food hygiene training.                                                                                                        | $p > 0.05$  |
| Practice  | (Adamu et al., 2021)           | Impact of An Intervention Program on Improvement of Knowledge, Attitudes, Practices (KAP) On Food and Occupational Health                                                   | Comparison of score in pre and post- intervention phases indicated no significant difference was                                                                                                    | $p = 0.115$ |

|          |                                |                                                                                                                                                       |                                                                                                                                                                                                                                                                   |           |
|----------|--------------------------------|-------------------------------------------------------------------------------------------------------------------------------------------------------|-------------------------------------------------------------------------------------------------------------------------------------------------------------------------------------------------------------------------------------------------------------------|-----------|
|          |                                | Safety Among Cattle Abattoir Workers in Malaysia.                                                                                                     | observed in practice scores.                                                                                                                                                                                                                                      |           |
| Practice | (Isara & Isah, 2009)           | Knowledge and practice of food hygiene and safety among food handlers in fast food restaurants in Benin City, Edo State                               | Food handlers who had worked for longer years in the fast food restaurants had better practice of food hygiene and safety.                                                                                                                                        | p = 0.036 |
| Practice | (Mohd Ishanuddin et al., 2019) | An Investigation of Knowledge, Attitude and Practice of Occupational Safety and Health (OSH) on Safety Climate at Workplace in Manufacturing Industry | For the workers that acquired good practice of safety at the workplace, increased in the aspect of practicing safety would directly increase the perception of workers on supervisor declarative practices on the safety and health policies implemented at work. | p < 0.01  |

## 2.4 THEORETICAL FRAMEWORK TO DEVELOP THEORY-BASED INTERVENTION MODULE ON OCCUPATIONAL SAFETY AND HEALTH AT FOOD PREMISE (TRIM-OSH)

There are numerous social cognitive theories available in health evaluation and behavioral prediction. Most theories discussed on how we could determine various related behaviors through the theory structure. However, the application of some theory or model is more suitable than the other in determining specific interventions

to modify such behaviors so that the desired behaviors can be predicted and performed (Clayton & Griffith, 2008). Thus, it is essential to understand the theoretical knowledge of particular behavior and behavioral change so that the potential efficacy of the developed intervention can be maximized. In essence, the theory will impart known knowledge on how individuals act and what are the moderators that may contribute to their actions, based on the nature of human behavior and other surrounding influences. In this research study, the application of theory being instilled as an integral part of the development of the intervention module, such as being recommended by the UK Medical Research Council's guidance for developing and evaluating complex interventions (Campbell et al., 2000).

#### **2.4.1 The Health Belief Model**

The Health Belief Model (HBM) is one of the most extensively used models of frameworks in the scientific research of health behavior. HBM provides a comprehensive understanding in explaining change and maintenance of desired health-related behaviors and a guiding framework for health behavior interventions. HBM consists of conceptual constructs that suggest why an individual comes to a point of action, for example, to prevent certain situations. The construct includes perceived susceptibility, which can be defined as belief about the likelihood of getting a disease or condition and becoming a threat, perceived severity, which can be defined as feelings about the seriousness of getting a disease or condition and becoming a threat if nothing was done, perceived benefits, which can be defined as an individual perceived benefits towards various action for diminishing the threat of the disease or condition, perceived barrier, which can be defined as the potential negative aspects of a particular action or practice, and self-efficacy, which defined as “the conviction that one can successfully execute the behavior required to produce the outcomes” (Bandura, 1997). HBM identified that besides sociodemographic and socioeconomic factors,

knowledge is an important modifying factor that influences individuals' beliefs and, subsequently, behaviors such as been depicted in the figure below.

[figure not shown]

Figure 1. The Health Belieff Model

Source: Adapted from Glanz, K., Rimer, B. K., & Viswanath, K. (Eds.). (2015)

## 2.4.2 The Theory of Reasoned Action

Theory of Reasoned Action (TRA) is one of the most commonly used theories of behavior and behavior changes across the social and behavioral sciences (Davis et. al., 2015). Based on TRA model, an individual decision to engage in specific desired behavior is determined by their attitude and social normative perceptions towards the behavior. In further elaboration, attitude can be defined as an individual's belief about the outcome of certain behavior. An individual with strong beliefs that positively valued outcome is more likely to perform the desired behavior and being referred to have a positive attitude towards the behavior. On the other hand, those with strong beliefs that negatively value outcome is less likely to perform the behavior and are said to have a negative attitude towards the behavior. As for subjective norm, it can be defined as the individual normative belief towards the outcome of certain behavior. Similarly, an individual who believes that certain

referents think they should perform a behavior and is motivated to meet the expectations of those referents will hold a positive subjective norm and vice versa.

[figure not shown]

Figure 2. Theory of Reasoned Action

Source: Adapted from Fishbein, M. & Ajzen, I. (1980)

### 2.4.3 The Tone's Health Action Model

The Tones' Health Action Model originated from the two models in health evaluations and behavioral predictions mentioned above, the Health Belief Model and the Theory of Reasoned Action (Frizelle, 1995).

[figure not shown]

Figure 3. Health Action Model

Source: Adapted from Goodman-Brown and Gottwald (2008) and Tones and Tilford (2001)

Based on this model, the normative system is considered central to all behavior, distinguishing between attitudes and beliefs, behavioral intentions, and resultant actions. Beliefs and attitudes may interact to produce a behavioral intention. The intention leads to an advocated action when appropriate social and environmental conditions prevail (Frizelle, 1995). Other influencing factors are also incorporated, for example, the knowledge about food hygiene obtained from a food hygiene course and the influence of norms, which could be influenced by the provision of support for changes in food handling practices from management and colleagues in the food industry; motivation to change behavior, belief system towards the occupational safety and health practice at the workplace, and the development of personal skills to apply the knowledge gained from a course (Seaman, 2010).

#### 2.4.4 Social Cognitive Theory

Social cognitive theory (SCT) was known as Social Learning Theory (SLT), developed by infamous psychology professor Albert Bandura in 1960s. SCT provides an understanding of how human beings are dynamically influenced and influenced by our surroundings. It also explains how human behavior is regulated through observational learning and modeling processes and the influence of self-efficacy on the production of behavior. The characteristics components of SCT include reciprocal determinism, which refers to the dynamic and reciprocal interaction of person, environment and behavior. The other elements of SCT are the behavioral capability of an individual to perform a preventive behavior, observational learning from others, reinforcement for continuing or discontinuing the behavior, outcome expectation, and self-efficacy, as being depicted below (Glanz et al., 2008).

[figure not shown]

Figure 4. Social Cognitive Theory

Source: Luszczynska, A., & Schwarzer, R. (2015)

### 2.4.5 Knowledge, Attitude, and Practice (KAP) Theory

The KAP theory is another well-known health behavior change theory that explains the nature of behavior change among individuals. KAP theory suggests that an individual's behavioral changes can be divided into three processes: the acquisition of knowledge, the generation of attitudes, and the formation of behavior. Under this theory, knowledge can be defined as an individual understanding of any topic. The understanding will allow the individual to receive, retain and use specific information that at times mixed with individual experience and skills (Badran, 1995; Kaliyaperumal, 2004). Attitude, on the other hand, can be defined as participants' belief about the topic and propensity to react in a definitive action when facing a certain situation (Badran, 1995; Kaliyaperumal, 2004), and practice refers to how an individual demonstrates their knowledge and attitude (Badran, 1995; Kaliyaperumal, 2004).

The KAP theory presents the progressive relationship among knowledge, attitudes, and behavior: Knowledge and attitude are the driving forces for the change in practice. Only when people understand health-related knowledge and establish a positive attitude is it possible to form correct practice.

[figure not shown]

Figure 4. KAP Theory

Source: Zeng et. al. (2019)

In this study, the SCT was observed to be appropriate in the development of a theory-based intervention module as it provides a strong construct on the personal factors, environmental factors and behavioral factors on occupational safety and health among food handlers. It is aligned with the HBM that identified knowledge as an important modifying factor that influences individuals' beliefs and behaviors. It also suits the KAP theory that suggests that the initial process towards behavioral change or change in practice is an acquisition of knowledge. On the other hand, TRA explained the role of attitude that been characterized by an individual's belief about the outcome (practice) of certain behavior. It is again aligned with KAP theory, that propose knowledge as the foundation of behavior change, and belief and attitudes are the driving force of behavior change. Thus, in this study, the SCT component has been used as the theoretical framework of the module development. The HBM and KAP theory will then be adopted in exploring the KAP on occupational safety and health at food premises among food handlers. The conceptual framework of the presented theory is shown in Figure 5.

Figure 5. Conceptual Framework of TRIM-OSH based on SCT to improve KAP on OSH among food handlers working at food premises in Selangor

[figure not shown]

## CHAPTER 3

### METHODOLOGY

#### 3.1 Study location

Due to MCO order imposed by the government on the verge of Covid-19 pandemic situation, 15% of the workers from the Services Sector reported that they had lost their job. The highest percentage of workers who lost their job were reported to come from the Food and Beverages industry at 35.4%, with 85.9% who remain in the industry reported having their income decreased with 61.6% reported having a reduction of more than 50%. In general, based on the DOSM special survey, 69.7% of workers who have been in the workforce for less than one year and 63.2% of those who have been in the workforce for a duration of 1-3 years were severely affected as they only have a financial saving that only, is able to survive for less than a month. This group of workers consists mainly of youth who just finish their education and enter the workforce from secondary or tertiary education at the age of 15-30-year-old.

In Malaysia, Selangor state has stood as the biggest contributor to Malaysia's GDP for years. Selangor is located on the right and west sides of Peninsular Malaysia, bounded by Perak in the north, Pahang in the east, Negeri Sembilan in the south, and Straits of Malacca in the West. Selangor has a total land area of 7,957km^2. The total population in Selangor is currently estimated at 6.53 million, with 3.40 million males and 3.13 million females. About 70% of the population are adults of age 20 and above. The average annual population growth rate in Selangor has decreased from 2016 to 2019, from 1.8% to 0.8%. Malay is the primary ethnicity with 3.60 million, followed by Chinese 1.57 million, Indian at 0.73 million, others 0.05 million, and non-Malaysian citizens 0.58 million. Selangor reported that it has achieved 91.4% urbanization in 2010 and is currently the most populous state in Malaysia (DOSM, 2021).

Regarding Covid-19 pandemic situation, Selangor recorded an increase in the unemployment rate among youth at 2.8% from 2019 to 2020 (6.1% to 8.9%), with the number of those who were unemployed in 2020 recorded at 101,800. This does not include adults outside the scope of youth from the age 15-30 but are still within the working range age up to 65-year-old. Considering these pieces of information, and the timing of the study duration, which will occur during the recovery period from post-Covid-19 pandemic where the food and beverages industry expected to catch up with the loss due to MCO, Selangor has been selected as the study location. The newly recruited labor force into the food and beverages industry in Selangor who undergo the compulsory Food Handler Training program as required by the ministry will also have the opportunity to involve in the formal training program on occupational safety and health provided during this research.

### **3.2 Study design**

The study is a randomized controlled trial study. A single blinded, cluster randomized controlled trial study design will be conducted with pre-assessment and post-assessment on the intervention module. The respondents will be divided into two groups, intervention or control. The control group will receive a standard treatment and brochures related to occupational safety and health, while the intervention group will receive a theory-based intervention module on occupational safety and health among food handlers. The duration of the study is within 3-6 months.

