**Methodology:**

The study is a single-blinded, cluster randomized controlled trial study, expected to be conducted from 1st December 2023 to 30th November 2024 among 139 registered food handlers in Selangor under municipal in the working-age between 18-65 years old. The respondents will be allocated into intervention and control group. The intervention group will receive TRIMOSH intervention while the control group will receive standard training. The data will be collected via self-administered questionnaires and has been analyzed using SPSS version 25.

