## **1.2 PROBLEM STATEMENT**

Since 1996, the Ministry of Health Malaysia (MOH) has launched the food handler training course to give exposure and awareness to food handlers on food safety, hygiene, self-hygiene, and premise hygiene, mainly to prevent food poisoning incidents in the country. Subsequently, under Food Hygiene Regulations 2009, all food handlers are compulsory to attend the Food Handler Training Programme organized by any school or institute that has been certified by MOH. Food handlers are defined as individuals who are (1) directly involved in the food preparation, (2) come into contact with food or food contact surfaces, and (3) handle packaged or unpackaged food, or appliances, on any food premises (Laws of Malaysia Act 281 Food Act, 2006). Under this regulation, any food handler who fails to undergo training or obtain a Certificate of Food Handlers Training shall be liable to a fine or compound not exceeding RM10,000 or imprisonment for a term not exceeding 2 years (Food Hygiene Regulation, 2009).

The food handler training module by MOH has been formalized and uniformed and comprises four sections: introduction, food hygiene, food safety, and critical factors of food poisoning (MOH, 2014). However, despite this module being compulsory, the data reported by the Department of Occupational Safety and Health (DOSH)

shows that the number of cases reported and cases confirmed for occupational poisoning and disease generally show a consistently increasing trend from 2010 to 2019.

Regarding occupational safety and health of workers who work as food handlers in Malaysia, they are generally governed and regulated by Act 514 Occupational Safety and Health (OSHA) Act 1994 as for any other occupations. It is within the spirit of the act to secure the safety, health, and welfare of persons at work to protect the workers and others from any risk or health implication associated with the activities of persons at work and prevent occupational diseases. An occupational disease is defined as any disease contracted due to exposure to risk factors arising from work activity (DOSH, 2021). However, there is currently no occupational safety and health training module, required or made compulsory by the government for food handlers to equip them with appropriate knowledge, attitude, and practice on occupational safety and health to prevent injuries and illnesses related to their work.

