### **1.5.2 SPECIFIC OBJECTIVE**

The specific objectives of this study are:

1. To describe the baseline sociodemographic, socioeconomic, working experience, training attendance, and means KAP score of food handlers.
2. To develop and implement a theory-based intervention module for food handlers in Selangor, Malaysia.
3. To evaluate the effectiveness of the SCT constructs as the main framework of the intervention module in improving KAP among food handlers between the intervention and control group.

4. To describe and compare the effectiveness of the TRIM-OSH on the change of knowledge, attitude and practice compared to standard training among food handlers between and within groups at the end, and one-month post training, after controlling for covariates.

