### **3.9 Data collection methods**

The data collection will occur in the selected districts in Selangor, Malaysia, within a given time frame. The questionnaire will be distributed to selected respondents in the selected Food Handler Training School. All participants who agree to participate in the study will be consented by agreeing to the agreement statement prior study begins. The questionnaire will be given in the Google Form format for the participants to access the form with the response collected immediately upon completion before and immediately after training. The participants will be contacted after one-month post-training for the reassessment of the KAP score. If the accessibility of the Google Form is not available, the same questionnaire in the hardcopy format will be given and collected on the same day at all mentioned events.

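### The comparator is standard training in the summary and Objective 4, but standard treatment plus occupational-safety brochures in Section 3.2, so the contrast under test is not fixed

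*Combined protocol and SAP*

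**What the plan says.** The comparator is described in three places.

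- Executive Summary, Methodology: "The intervention group will receive TRIMOSH intervention while the control group will receive standard training".
- Section 1.5.2, Objective 4: the effect is to be assessed "compared to standard training among food handlers between and within groups at the end, and one-month post training, after controlling for covariates".
- Section 3.2, Study design: "The control group will receive a standard treatment and brochures related to occupational safety and health". For the other arm, that section names only the TRIM-OSH module and is silent on brochures.

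The first two mention no brochures. The third does, and it replaces training with treatment, a term the plan does not define. No other section of the available text mentions the brochures.

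Section 1.2 says that the compulsory Ministry of Health course "comprises four sections: introduction, food hygiene, food safety, and critical factors of food poisoning", and adds that no occupational safety and health module is currently required of food handlers. Section 3.9 has the questionnaire completed "before and immediately after training" and again one month later.

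**The concern.** The brochures cover the subject on which participants are scored, so their presence in the control arm bears directly on the outcome. The existing course lists no section devoted to occupational safety, and the brochure may be the only dedicated material on that subject that controls receive.

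The choice of comparator decides what the trial can conclude. Section 1.3 says that the results may help the government add an occupational-safety component to the current course. That use calls for a comparison with the current course. A comparison with the current course plus a brochure answers a different question, and once brochures have been handed out during follow-up no analysis can recover the first one.

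**Working it through.** No figure in the plan depends on this point, so the check is mainly a comparison of texts.

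**Step 1: what each arm receives, by source**

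| Source | Control | Intervention |
|---|---|---|
| Executive Summary | Standard training | TRIM-OSH |
| Objective 4 | Standard training | TRIM-OSH |
| Section 3.2, Study design | Standard treatment (undefined) and brochures | Module; brochures neither given nor excluded |
| Intervention Module Outline | Not described | Web course, slides, video, quiz; no brochure listed |
| Section 3.5 | Recruited among people attending the food handler course | Same |

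Section 3.5 makes it likely that both arms take the standard course, although the plan does not list it as part of the intervention arm.

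**Step 2: the contrast under each reading**

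Assume that both arms take the standard course. Let *m* be the score gain from the module over that course, and *b* the gain from the brochure over that course.

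- No brochures before the last questionnaire: the difference is *m*. This is Objective 4 as worded.
- Brochures to controls only, during follow-up: the difference is *m* − *b*, a fraction *f* = 1 − *b*/*m* of the Objective 4 effect. If the brochure teaches anything relevant, *f* is below 1.
- Brochures to both arms: the difference is the gain from the module in people who also have the brochure. It equals *m* only if the two do not overlap in what they teach.

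Only the first reading matches Objective 4, and Section 3.2 does not say that brochures are held back.

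**Step 3: can the size be computed?**

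It cannot. Section 3.6 (Sample size) gives clusters, participants per cluster and attrition, but no effect size, standard deviation, intracluster correlation or power. Nothing in the plan gives *b* or *m*.

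**Step 4: illustration under assumptions**

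Take alpha 0.05 (Section 3.10), assume that it is two-sided, assume a planned power of 80% or 90%, and assume that brochures remove 10%, 20% or 30% of the true difference. By the normal approximation, power = Φ[*f* × (1.960 + z_power) − 1.960], with z_power = 0.842 for 80% and 1.282 for 90%.

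| Share removed | *f* | From 80% | From 90% |
|---|---|---|---|
| 10% | 0.9 | Φ(0.9 × 2.802 − 1.960) = 71% | Φ(0.9 × 3.242 − 1.960) = 83% |
| 20% | 0.8 | Φ(0.8 × 2.802 − 1.960) = 61% | Φ(0.8 × 3.242 − 1.960) = 74% |
| 30% | 0.7 | Φ(0.7 × 2.802 − 1.960) = 50% | Φ(0.7 × 3.242 − 1.960) = 62% |

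The shares removed are assumptions. The table shows how sensitive power would be and does not estimate the loss in this trial.

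**The case against.** The strongest reply is that this is loose wording and that standard training plus a leaflet is a legitimate control. H4 and H04 in Section 1.6 refer only to the intervention and control groups, and the general objective names no comparator. If the brochure works, the error most likely runs against the module, so a false positive is not the worry. Section 2.3 also acknowledges that existing food-safety training contains some occupational-safety content, such as hand washing, so standard training is not free of outcome content. The research flow chart (Figure 6) and the information sheet are not available here and may say more about what each arm receives.

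Much of this stands. It lowers confidence about how sharp the contrast between the two comparators is, and it shows the likely direction of error. It does not remove the contradiction. Objective 4 and the summary do name a comparator, and Section 3.2 names another. An error that runs against the module still matters, because a useful programme could look weak.

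A reader might infer that the intervention arm is denied brochures. That is the natural reading of Section 3.2, which sets the arms against each other and assigns brochures to one, and the module outline lists none. But it rests on silence. The same sentence also omits the standard course from the intervention arm, so it is not a complete list.

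A reader might also infer that the module's effect would appear to fade by one month as controls read their brochures. This assumes a hand-out time that the plan does not state. The within-group results called for in Objective 4 and Section 3.10 would show control scores rising, and Section 3.6.1 defines maintenance from baseline to endpoint, not from the immediate test to one month.

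**Conclusion.** The comparator is defined in two incompatible ways, and nothing in the available text reconciles them. Following Section 3.2 during follow-up would compare TRIM-OSH with an enhanced control and most likely give a smaller difference than the contrast in Objective 4.

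The direction rests on two assumptions: that the brochure conveys something the questionnaire scores, and that controls have it before a post-training assessment while the intervention arm does not. The size of the shrinkage cannot be derived from the plan.

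It would go too far to say that the trial cannot test its stated contrast. It still compares TRIM-OSH with a control condition, and if brochures are held back until the last questionnaire, Objective 4 stands as written. What the plan leaves open is which control condition that is.

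**What to change.** Reconcile the Executive Summary, Objective 4 and Section 3.2 to one comparator. For each arm, state whether it receives the standard course, the brochure and the module, and when. Make TRIM-OSH the only difference between arms at both post-training assessments. Two arrangements do this:

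1. Withhold brochures from both arms until the one-month questionnaire is returned, and keep Objective 4 as worded. The cost is a later hand-out.
2. Give the same brochure to both arms at the same time as the training, before the immediate post-test, and restate Objective 4 as TRIM-OSH added to standard training plus brochure. The cost is brochures for the second arm and a slightly more active comparator.

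Handing brochures to both arms between the immediate post-test and the one-month assessment should be avoided. The immediate test would then compare the arms without brochures and the one-month test with them, so the contrast would change between time points.

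Either arrangement needs only protocol wording and a hand-out schedule, and should be settled before any brochure is distributed.
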